#### 5.2.2.2 Adverse event and serious adverse event reporting

All adverse events, serious and non-serious, occurring during the course of the clinical trial (i.e., from signing the informed consent onwards through the observational phase) will be collected, documented and reported to the sponsor by the investigator on the appropriate CRFs / eCRFs / SAE reporting forms. Reporting will be done according to the specific definitions and instructions detailed in the 'Adverse Event Reporting' section of the Investigator Site File.

For each AE, the investigator will provide the onset date, end date, intensity, treatment required, outcome, seriousness, and action taken with the investigational drug. The investigator will determine the relationship of the investigational drug to all AEs as defined in Section 5.2.2.1.

Clinically relevant abnormalities found during the physical examination at Visit 1 (including abnormalities with vital signs or ECG) will be considered to have already existed prior to signing of informed consent and therefore should be considered baseline conditions instead of adverse events, unless there is good reason to assume that they first appeared after signing of informed consent.

The investigator also has the responsibility to report AEs occurring within one week after a subject completes the trial. Any AEs reported to the sponsor during this period must be documented in the safety database.

If not stipulated differently in the ISF, the investigator must report the following events via telephone/fax using the SAE form immediately (within 24 hours or the next business day whichever is shorter) to the sponsor: SAEs and non-serious AEs occurring at the same time as an SAE and/or which are medically related to the SAE(s), and protocol-specified significant events. With receipt of any further information to these events, a follow-up SAE report has to be provided. SAEs and non-serious AEs must include a causal relationship assessment made by the investigator.

The SAE form is to be forwarded to the defined unique entry point identified for the BI OPU (country-specific contact details will be provided in the ISF). This immediate report is required irrespective of whether the investigational product has been administered or not and irrespective of causal relationship. It also applies if new information to existing SAEs or protocol-specified significant events becomes available.

### Pregnancy

In rare cases, pregnancy might occur in clinical trials. Once a female subject has been enrolled into the clinical trial, after having taken study medication, the investigator must report immediately any drug exposure during pregnancy to the sponsor. Drug exposure during pregnancy has to be reported immediately (within 24 hours or next business day

Proprietary confidential information.

© 2012 Boehringer Ingelheim International GmbH or one or more of its affiliated companies. All rights reserved.

This document may not - in full or in part - be passed on, reproduced, published or otherwise used without prior written permission.

whichever is shorter) to the defined unique entry point for SAE forms of the respective BI OPU (country-specific contact details will be provided in the ISF). The outcome of the pregnancy associated with the drug exposure during pregnancy must be followed up. In the absence of an (S)AE, only the Pregnancy Monitoring Form for Clinical Trials and not the SAE form is to be completed. The ISF will contain the Pregnancy Monitoring Form for Clinical Trials (Part A and Part B).

### 5.2.3 Assessment of safety and efficacy laboratory parameters

All safety and efficacy laboratory samples will be collected according to the summary of laboratory assessments based on Table 5.2.3: 1 (below). Collection of samples after a full overnight fast (nothing to eat or drink except water for at least ten hours) and before administration of BI 10773 25 mg will be required at indicated visits. Subjects should continue to take their insulin regimen as instructed by the prescribing physician.

All parameters that will be determined during the trial conduct are listed in Table 5.2.3: 2 and 5.2.3: 3. The analyses will be performed as available by a certified ~~local~~ laboratory. Lab values will be entered in eCRFs, as applicable.

Table 5.2.3: 1 Summary of laboratory assessments

| Visit 1                                                                                                              | Visit 2                                                                             | Visit 3
(Clamped
euglycaemia)                                                           | Visit 4
(Clamped
Hyper-
glycaemia)              | Visit 8                                                                   | Visit 11                                                                            | Visit 12
(Clamped
euglycaemia)                                                       | Visit 13
(Clamped
Hyper-
glycaemia)                       | (EOT)                                                                                                 | Visit 15*                                                      |
|----------------------------------------------------------------------------------------------------------------------|--------------------------------------------------------------------------------------------|-----------------------------------------------------------------------------------------------|----------------------------------------------------------|---------------------------------------------------------------------------|--------------------------------------------------------------------------------------------|--------------------------------------------------------------------------------------------|--------------------------------------------------------------------|-------------------------------------------------------------------------------------------------------|----------------------------------------------------------------|
| Day
-21                                                                                                           | Day
-14                                                                                 | Day
1                                                                                      | Day
2                                                 | Day
29                                                                 | Day
50                                                                                  | Day
57                                                                                  | Day
58                                                          | Only for early
discontinued
subjects (after
start of
therapy)                             | Day
72                                                      |
| Non-
Fasted                                                                                                       | Fasted                                                                              | Non-
Fasted                                                                                | Non-
Fasted                                           | Non-
Fasted                                                            | Fasted                                                                              | Non-
Fasted                                                                             | Non-
Fasted                                                     | Fasted                                                                                         | Non-
Fasted*                                                |
| HbA 1c
Hematology
Chemistry
TSH
Urine A/B
Urine:
albumin and
creatinine
Serum hCG | FPG
HbA 1c
GA FA
Hematology
Chemistry
Lipids
Urine A/B | HbA 1c
GA FA
Hematology
Chemistry
Renal panel
Urine
A/B/C | Hematology
Chemistry
Renal panel
Urine
A/B/C | HbA 1c
GA FA
Hematology
Chemistry
Urine A/B | FPG
HbA 1c
GA FA
Hematology
Chemistry
Lipids
Urine A/B | HbA 1c
GA FA
Hematology
Chemistry
Renal panel
Urine A/B/C | Hematology
Chemistry
Renal panel
Urine A/B/C
Serum hCG | FPG
HbA 1c
GA FA
Hematology
Chemistry
Lipids
Urine B
Serum hCG | HbA 1c
GA FA
Refer to
Note
below |
|                                                                                                                      |                                                                                            |                                                                                               |                                                          | Pre-dose
PK                                                            | Pre-dose
PK (same
time as
V8)                                                     | Pre-dose
PK (same
time as
V8)                                                     |                                                                    |                                                                                                       |                                                                |

**\*Note for Visit 15:** If required, other panels/tests may be repeated (fasted measurements as needed) based on clinically significant findings at Visits 11-13 or per investigator judgement.

Proprietary confidential information.

© 2012 Boehringer Ingelheim International GmbH or one or more of its affiliated companies. All rights reserved.

This document may not - in full or in part - be passed on, reproduced, published or otherwise used without prior written permission.

Table 5.2.3: 2                      Safety and efficacy laboratory parameters – whole blood, serum or plasma

---

**Hematology:**

- Haematocrit
- Hemoglobin
  - Reticulocyte Count (if hemoglobin is outside normal range)
- Red Blood Cells (RBC) / Erythrocytes
- White Blood Cells (WBC) / Leukocytes
- Platelet Count / Thrombocytes
- Differential Automatic (absolute count):
  - Neutrophils, Eosinophils, Basophils, Monocytes, Lymphocytes

---

**Clinical chemistry:**

- Albumin
- Alkaline phosphatase (AP)
- ALT (alanine aminotransaminase, SGPT)
- AST (aspartate aminotransaminase, SGOT)
- Bicarbonate
- Bilirubin
- Calcium
- Chloride
- Creatinine
- Creatine kinase
- Troponin
- Lactate dehydrogenase
- Lipase
- Magnesium
- Phosphate
- Potassium
- Protein total
- Sodium
- Urea
- Uric acid

---

**Lipids:**

- Cholesterol (total)
  - HDL cholesterol
  - LDL cholesterol
  - Triglycerides
- 

Proprietary confidential information.

© 2012 Boehringer Ingelheim International GmbH or one or more of its affiliated companies. All rights reserved.

This document may not - in full or in part - be passed on, reproduced, published or otherwise used without prior written permission.

Table 5.2.3: 2 (cont'd) Safety and efficacy laboratory parameters – whole blood, serum or plasma (Page 2 of 2)

---

**Renal panel:**

- cGMP
- Nitric oxide
- Angiotensin II (RAAS mediator)
- Angiotensinogen (RAAS mediator)
- Aldosterone (RAAS mediator)
- Plasma renin activity (RAAS mediator)
- Plasma renin concentration (RAAS mediator)
- Inulin
- Paraaminohippurate (PAH)
- Adrenaline
- Noradrenaline
- Cystatin C
- Erythropoietin

**Other assessments at selected visits:**

- Thyroid stimulating hormone (TSH)
- Glycated hemoglobin (HbA1c)
- ~~Glycated albumin (GA)~~
- **Fructosamine (FA)**
- Fasting plasma glucose (FPG)
- Human Chorionic Gonadotropin (hCG)\*

---

\*Pregnancy testing (serum) will be performed in female subjects of child bearing potential at Visit 1 and Visit 13 or EOT (based on the Summary of Laboratory Assessments table in Section 5.2.3). Additional tests may be done if locally required and per Investigator judgement.

Table 5.2.3: 3 Safety and efficacy laboratory parameters - urine

---

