| 13:30-14:00 | Repeat measurements of MAP, GFR, ERPF, FF, RBF and RVR (all average of 2 measurements), RAAS mediators, NO, prostanoids, arterial stiffness and markers of sympathetic nervous system activation (heart rate variability and circulating plasma levels of adrenaline/noradrenaline) and other laboratory assessments.                                                                  |

- E. In addition to the required ECG at Visit 1 and Visit 13, additional ECGs should be performed in cases of cardiac symptoms (rhythm disorders or cardiac ischemia).
- F. Subjects will be advised to follow a healthy diet and exercise program based on investigator recommendations during the study except during the 7 days preceding the start of renal physiology laboratory assessments when they will be instructed to follow a modified diet, refer to G below for details.
- G. Subject will be instructed to adhere to a high-sodium (preferably > 140 mmol/day) and moderate-protein (<1.5g/kg/day) diet during the 7 days preceding the start of renal assessments at baseline during Visits 3 and 4 (the diet to continue until the end of renal assessments at baseline, Visit 4) and during the 7 days preceding the start of the end of treatment renal assessments during Visits 12 and 13 (the diet to continue until the end of renal assessments). The initial 8-point HBGM must be performed prior to start of the modified diet (i.e. prior to day -7). If a subject fails to adhere to the prescribed high-sodium and moderate-protein diet, the investigator will assess whether the subject is still eligible to start the renal assessments based on the subject's actual diet during the 7 days preceding Visit 3. In cases of an unsatisfactory diet, subjects may have to be screen failed based on the investigator's judgement.

Proprietary confidential information.

© 2012 Boehringer Ingelheim International GmbH or one or more of its affiliated companies. All rights reserved.

This document may not - in full or in part - be passed on, reproduced, published or otherwise used without prior written permission.

- H. A local pregnancy test will be done in women of child bearing potential. More frequent testing can be done if required by the local regulation and/or authority or per investigator judgement.

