- L. To demonstrate the desired sodium excretion level (preferably > 140 mmol/day) following the prescribed high-sodium / moderate-protein diet, the site is to remind the subject to perform a 24-hour urine collection on study Days -1 (collection period from day -1 to day 1) and 56 (collection period from day 56 to 57), hence the collection of urine to start the day before clamped procedures are performed and to end the morning of Visit 3 and Visit 12. It is expected that subjects would achieve a urinary sodium excretion rate > 140 mmol/day after following the prescribed high-sodium / moderate-protein diet for 7 days. Daily diet compliance will be captured by the subject in study-specific logs. In addition to sodium; glucose, urea and creatinine will also be measured in the 24-hour urine sample.
- M. For treatment satisfaction, the Diabetes Treatment Satisfaction Questionnaire will be used in its status version (DTSQs) and data will be collected in eCRFs.
- N. Subjects should start taking the placebo run-in medication in the morning (7-11 AM) of the day following Visit 2 and continue daily intake until Visit 3. Subjects must bring to the clinic Visit 3 all previously dispensed medication and packaging.

Proprietary confidential information.

© 2012 Boehringer Ingelheim International GmbH or one or more of its affiliated companies. All rights reserved.

This document may not - in full or in part - be passed on, reproduced, published or otherwise used without prior written permission.

- O. The trial medication (BI 10773) will be dispensed at the end of Visit 4 (study Day 2). Subject will be instructed to start taking the trial medication (BI 10773 25 mg tablet once daily) as of the morning of study Day 3. Subjects should continue to take the study drug daily at the same time every day (7-11 AM). Subject will be reminded not to take the trial medication the morning of clinic Visits 8, 11, 12 and 13. During study Visits 12 and 13, BI 10773 dosing will be done at the clinic approximately 1.5 hours before the start of the planned renal assessments at around 12:00 (refer to footnote D for details). The PK samples for Visits 11 and 12 should be collected at **approximately** the same time as Visit 8.

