### 3.3.2 Inclusion criteria

1. Male or female subject diagnosed with T1DM at least 12 months prior to informed consent
2. Age  $\geq 18$  years
3. Signed and dated written informed consent by date of Visit 1 in accordance with GCP and local legislation
4. HbA1C of 6.5% to 11.0% at Visit 1 (no more than 5 subjects with an HbA1C between 6.5% to <7.0% will be included)
5. BMI (Body Mass Index) of 18.5 kg/m^2 to 35.0 kg/m^2 at Visit 1 (Screening)
6. Subjects must be either:
  - experienced insulin pump users ( $\geq 3$  months of use prior to Visit 3 and willing to use the same insulin pump during the course of the study) or
  - be on multiple daily injections (MDI) of any type of insulin (and be willing to continue on MDI therapy during the course of the study)
7. Subjects must follow an established and individualized carbohydrate counting method and an insulin titration algorithm based on investigator recommendations
8. Subjects must have had a stable glycaemic status defined by their latest HbA1C value as measured 2-12 months prior to screening which must be within 1.5% of the baseline screening value (Visit 1)
9. Subjects must have an eGFR  $\geq 60$  ml/min/1.73m^2 at screening
10. Subject must be able and willing to perform study assessments

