17. Blood dyscrasias or any disorders causing hemolysis or unstable red blood cells (e.g. malaria, babesiosis, hemolytic anemia)
18. Pre-menopausal women (last menstruation  $\leq$  1 year prior to informed consent) who:
  - a. are nursing or pregnant or
  - b. are of child-bearing potential and are not practising an acceptable method of birth control, or do not plan to continue using this method throughout the study and do not agree to submit to periodic pregnancy testing during participation in the trial. Acceptable methods of birth control include tubal ligation, transdermal patch, intra uterine devices/systems (IUDs/IUSs), oral, implantable or injectable contraceptives, sexual abstinence, double barrier method and vasectomised partner

Proprietary confidential information.

19. Participation in another trial with an investigational drug within 30 days prior to informed consent
20. Alcohol or drug abuse within the three months prior to informed consent that would interfere with trial participation based on investigator judgement or any ongoing clinical condition that would jeopardize subject safety or study compliance based on investigator judgement

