### **3.3.4 Removal of subjects from therapy or assessments**

#### **3.3.4.1 Removal of individual subjects**

An individual subject is to be withdrawn from the trial if:

- The subject withdraws consent, without the need to justify the decision
- The subject needs to take concomitant drugs that interfere with the investigational product or planned study assessments
- The subject is no longer able to participate for other medical reasons (e.g. surgery, AEs or other diseases)
- Occurrence of hypoglycaemia that may put the subject at risk with continued participation (e.g. repeated hypoglycaemic episodes) based on investigator judgement
- If a subject becomes pregnant during the trial the investigational drug will be stopped, the subject will be discontinued from the trial and the subject will be followed up until birth or otherwise termination of the pregnancy.

A subject can be discontinued after discussion between sponsor and investigator if eligibility criteria are being violated, or if the subject fails to comply with the protocol (e.g. non-attendance at study assessments).

Subjects who drop out during the screening phase and before the start of treatment with BI 10773 (study Day 3) will be considered as screening failures. They have to be recorded as a screening failure in the electronic Case Report Forms (eCRFs) and no further follow-up is required.

Subjects who discontinue or withdraw from the study after study Day 3 (after the start of therapy) will be considered as “early discontinuations” and the reason for premature discontinuation will be recorded in the eCRFs. Subjects who discontinue prematurely (before completion of Visit 13) will be replaced in order to obtain at least 12 subjects in the hyperfilterer group and 12 in the non-hyperfilterer group who complete the treatment phase of the study (Visit 13). The data for screen failures will be included in the trial database and will be reported. A new antidiabetic medication regimen can be started immediately after discontinuation, if determined by the investigator as necessary for subject safety. This must be recorded in the eCRFs.

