From the start of the placebo run-in period (Visit 2), subjects should be instructed to take their trial medication once daily with water in the morning between 7:00 AM – 11:00 AM, except during study days 57 and 58 when the trial medication will be given at a later time as specified in the study Flow Chart (around 12:00 PM). To ensure a dose interval of approximately 24 hours, the medication should be taken at the same time every day. If a dose is missed by more than 12 hours, that dose should be skipped and the next dose should be taken as scheduled. On the day prior to a visit, the dose should be taken 22-26 h before the planned dose at the visit (except for Visit 12 and Visit 13 when subject will be dose at the clinic 1.5 hours before the start of renal assessments). No double doses should be taken and dose reductions are not permitted. BI 10773 can be taken with or without food. The first dose of BI 10773 will be taken in the morning of study Day 3 after baseline renal assessments have been completed (after Visit 3 and Visit 4). Thereafter, subjects will be instructed to take

Proprietary confidential information.

© 2012 Boehringer Ingelheim International GmbH or one or more of its affiliated companies. All rights reserved.

This document may not - in full or in part - be passed on, reproduced, published or otherwise used without prior written permission.

one tablet of BI 10773 25 mg daily in the morning. The last dose of BI 10773 will be administered 1.5 hours prior to renal assessments at Visit 13.

Subjects should be instructed not to take their trial medication on the morning of study clinic visits as they will be dosed at the clinic if required. Visits should be routinely scheduled in the morning, at approximately the same time of day (07:00 AM to 11:00 AM) for each visit (except Visits 3, 4, 12 and 13). The actual date and time of administration of the medication at the trial visit will be recorded in the eCRF.

The investigator or delegate may choose any available kit number for dispensing. A run-in medication kit should only be dispensed during the run-in phase and a treatment kit should only be dispensed to an eligible subject once the subject has completed the run-in phase and is still eligible for the study. The visit boxes from the same treatment medication kit should be dispensed to a subject at Visit 4 and Visit 8. All medication kit numbers will be recorded in eCRFs.

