#### 4.2.2.2 Restrictions on diet and life style

At the beginning of the Run-in period (i.e. at Visit 2), subjects will receive diet and exercise counselling by the Investigator or a member of the clinic staff. The counselling will be based on local diet recommendations for subjects with T1DM in consideration with each subject's possible concomitant illnesses. Site specific tools may be used to help subjects with diet and life style / exercise counselling. The subjects will be reminded to follow the recommended diet and exercise plan during the study. Subject are also requested to adhere to a specific high-sodium (preferably > 140 mmol/day) and moderate-protein (< 1.5 g/kg/day) diet only during the 7 days preceding the start of renal physiology laboratory assessments (respectively 7 days before study Days 1-2 and 57-58). Details of this specific diet will be given to subjects at Visit 2 and subjects will be reminded to re-start this diet at Visit 11.

Women of child-bearing potential must continue to practice an acceptable method of birth control (in accordance with the trial exclusion criteria [Section 3.3.3](#)) throughout the duration of the study including the follow up period.

Subjects should also not take part in another clinical trial involving an investigational medicinal product within the last 30 days before the date of informed consent for this trial.

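### Pregnancy is tested only at screening (Day -21) and on the last-dose day, so no scheduled test guards the first dose or can stop the drug before 55 of 56 doses are taken

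*Protocol*

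**What the plan says.** The footnote to Table 5.2.3: 2 fixes the test times: "Pregnancy testing (serum) will be performed in female subjects of child bearing potential at Visit 1 and Visit 13 or EOT". The pregnancy-test row of the flow chart, the laboratory table under flow-chart footnote K and Table 5.2.3: 1 show the same. Visits 2, 3, 4, 8, 11 and 12 all include a blood draw, but none lists hCG, and urine panels A, B and C do not contain it.

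Extra tests are permitted but not placed at any visit. Footnote H says: "More frequent testing can be done if required by the local regulation and/or authority or per investigator judgement".

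The rules that depend on pregnancy status are these:

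- Exclusion 18a (section 3.3.3) excludes pregnant women, and the flow chart repeats the eligibility check at Visits 2, 3 and 4.
- Section 4.1.4 allows a treatment kit to be dispensed only "once the subject has completed the run-in phase and is still eligible for the study". Dispensing is at the end of Visit 4 (Day 2), and the first dose is on Day 3.
- Section 3.3.4.1: "If a subject becomes pregnant during the trial the investigational drug will be stopped".
- Section 4.2.2.2: "Women of child-bearing potential must continue to practice an acceptable method of birth control".
- Exclusion 18b refers to women who do not plan to continue contraception "and do not agree to submit to periodic pregnancy testing during participation in the trial".

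**The concern.** Two of the protocol's own safeguards have no scheduled test behind them.

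The first is the check before dosing. A pregnancy that begins after the Visit 1 sample, or is too early for that sample to detect, meets exclusion 18a. Nothing scheduled between Day -21 and the first dose would reveal it. The eligibility check at Visits 2 to 4 then rests on what the woman knows or suspects.

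The second is the stop-drug rule. No hCG is scheduled between the first dose and Visit 13, the day of the last dose. The EOT test cannot trigger the rule, because EOT applies only to subjects who have already discontinued. Until Visit 13, detection depends on self-report, on the adverse-event questions at visits and calls, or on a discretionary test.

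At stake is fetal exposure for almost the whole 8-week course in a woman whose pregnancy goes unrecognised. In a completer, the single scheduled on-treatment test could document that exposure but could hardly limit it. A schedule with one test after screening also sits poorly with the periodic testing that exclusion 18b describes.

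**Working it through.** **Inputs (all from the protocol)**

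- Scheduled hCG: Visit 1 (Day -21) and Visit 13 (Day 58), or EOT after early discontinuation. Flow chart; section 5.2.3.
- First dose on Day 3; last dose at Visit 13; one tablet daily. Section 4.1.4.
- Day -1 is followed directly by Day 1, from the 24-hour urine collection period in flow-chart footnote L. There is no Day 0.
- Visit 8 on Day 29 ±4. Visit 12 on Day 57 ±4, with Visit 13 one day later. Flow chart.
- Treatment period of 8 weeks. Synopsis.

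**Check on the plan's own figure.** Nominal doses = last day − first day + 1 = 58 − 3 + 1 = 56 = 8 × 7. The stated 8 weeks is reproduced.

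**Current schedule**

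- Last scheduled test to first dose, Day -21 to Day 3: 20 days to Day -1, 1 to Day 1 and 2 to Day 3, total **23 days** (24 if a Day 0 were counted). This is not a ceiling, because Visit 2 is only preferred, not required, within a week of Visit 1.
- Doses before the Visit 13 dose, Days 3 to 57: 58 − 3 = **55 of 56**.
- With the Visit 12 window, Visit 13 falls on Days 54 to 62. At Day 54 there are 52 doses, 51 of them earlier. At Day 62 there are 60 doses, 59 of them earlier. The range is 51 of 52 to 59 of 60.
- Interval between the two scheduled tests: 20 + 1 + 57 = **78 days** (79 with a Day 0).

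The figure of 55 assumes that the Visit 13 result is known before that day's dose at about 12:00. If it is not, every dose has been taken.

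**With hCG added at Visit 3 (Day 1) and Visit 8 (Day 29)**

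- Visit 3 test to first dose: 3 − 1 = 2 days.
- Doses before the Visit 8 dose: 29 − 3 = 26 of 56. For Visit 8 on Days 25 to 33 the count is 22 to 30.
- Doses still avoidable after a positive Visit 8 test: 56 − 26 = 30 (54%) if the result precedes that day's dose, or 29 (52%) if it arrives the next day.
- Gaps between tests: Day -21 to Day 1 = 20 + 1 = 21; Day 1 to Day 29 = 28; Day 29 to Day 58 = 29. The longest is 29 days.

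| | Current | With Visits 3 and 8 |
|---|---|---|
| Last test to first dose (days) | 23 | 2 |
| Doses before first on-treatment test | 55 of 56 | 26 of 56 |
| Longest gap between tests (days) | 78 | 29 |

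**The case against.** The strongest case is that this is a consistent and deliberate design choice.

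- **The schedule agrees with itself.** All four places match, and the first global amendment revised the pregnancy-test entries, so the timing was looked at. The protocol nowhere promises a test at dispensing or a monthly test. This stands: the point is a weak safeguard, not a contradiction between sections.
- **Section 2.3 gives a rationale.** Rat and rabbit studies showed no effect on fertility or early embryonic development up to 300 mg/kg, and women are admitted on that basis if they use contraception. This lowers the expected harm and argues against a graver rating. The protocol nevertheless keeps the exclusion and the stop rule, so it does not itself treat those data and contraception as enough.
- **Remaining eligible need not mean repeating every screening test.** HbA1c, BMI and eGFR are fixed at screening. That is fair for those criteria. Pregnancy differs, because it can begin during the run-in and a later onset requires the drug to be stopped.
- **Extra tests and contact are available.** Footnote H covers local requirements as well as investigator judgement. There are also daily calls on Days 3 to 7, weekly calls and a Visit 8 examination. A pregnancy may well be recognised earlier by these routes, but none of them guarantees an assay.
- **The counts measure exposure, not risk.** The number of women of child-bearing potential is not given, so no absolute risk can be calculated. Nothing here touches the primary endpoint or the sample size. Both points stand.

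**Conclusion.** The concern holds as a patient-safety weakness in the schedule that should be corrected. As written, no scheduled test excludes pregnancy within the 23 nominal days before first dosing. None can trigger the stop-drug rule until 55 of 56 nominal doses have been taken (51 of 52 to 59 of 60 across the visit window).

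The figures rest on nominal visit days, no Day 0, one dose daily and a Visit 13 result available before that day's dose. They describe scheduled tests only and do not predict when a pregnancy would in practice be noticed. The proposed change removes most of the gap in days, but only about half of the doses before the first on-treatment test. A pregnancy beginning after Visit 8 would still wait until Visit 13 for a scheduled test.

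**What to change.** For women of child-bearing potential, add serum hCG to the existing blood draws at two visits:

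- **Visit 3**, with the result required before dispensing at the end of Visit 4.
- **Visit 8**, with the result required before, or promptly after, the second dispensing.

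Keep the Visit 13 or EOT test; a test at Visit 15 is optional. Update the flow chart, the footnote K table, Table 5.2.3: 1 and the footnote to Table 5.2.3: 2.

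As a separate wording correction, which adds no weight to the point, replace *and* with *or* before the testing clause in exclusion 18b, so that refusing tests excludes on its own. This matches inclusion 10 ("Subject must be able and willing to perform study assessments") and the contraception requirement in section 4.2.2.2.

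The cost is a protocol amendment and two assays per woman of child-bearing potential: at most 2 × 30 = 60 assays if all 30 subjects were such women. No visit or venepuncture is added.
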